### 8.3 Randomization and Stratification

There will be no randomization. Subjects will be stratified by age (at least 40 subjects per group):

- Group 1:  $\geq 4$  years to  $< 9$  years
- Group 2:  $\geq 9$  years to  $< 18$  years
- Group 3:  $\geq 18$  years to  $< 25$  years

### 8.4 Sample Size and Accrual

Approximately 140 children and youth, aged  $\geq 4$  years to 25 years old, who were infected with HIV-1 via perinatal transmission will be enrolled into this study. We will enroll at least 40 subjects each from three different age groups: age  $\geq 4$  years to  $< 9$  years of age,  $\geq 9$  years to  $< 18$  years of age and  $\geq 18$  to  $< 25$  years of age. This sample size is expected to yield at least 120 evaluable\* subjects, which will provide reasonably precise estimates of rates of adverse events and immunogenic response. Evaluable subjects are defined as having received two doses of Novartis **Influenza A (H1N1) 2009 monovalent vaccine** 21-28 days apart and had all HAI samples for collected up to and including Day 10 post second dose within the protocol specified windows.

Accrual is anticipated to be 4-6 weeks.

\*Evaluable subjects are defined as having received two doses of Novartis **Influenza A (H1N1) 2009 monovalent vaccine** 21-28 days apart and had all HAI samples for collected up to and including Day 10 post Dose #2 within the protocol specified windows.

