**NOTE: A dose is defined as TWO separate 15mcg intramuscular (IM) vaccine injections, totaling 30mcg**

### SAMPLE SIZE:

140 children and youth to obtain at least 120 evaluable\* subjects

\*Evaluable subjects are defined as having received two doses of **Influenza A (H1N1) 2009 Monovalent Vaccine** 21-28 days apart and had all HAI samples collected up to and including Day 10 post Dose #2 within the protocol specified windows.

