### STRATIFICATION:

Subjects will be stratified by age (at least 40 evaluable subjects per group)  
Group 1:  $\geq 4$  years to  $< 9$  years  
Group 2:  $\geq 9$  years to  $<18$  years  
Group 3:  $\geq 18$  years to  $< 25$  years

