This study will assess the safety and immune response following each of the two doses of Novartis **Influenza A (H1N1) 2009 monovalent vaccine** in HIV-1 infected children and youth in the US and Puerto Rico. Two doses are thought to be required because study subjects have had no prior exposure to **2009 H1N1 Influenza A**. Because seasonal influenza vaccine often results in blunted response in HIV-1 infected persons, we have opted to investigate the higher dose of antigen, 30mcg, in comparison to the 15mcg dose that is currently being studied in ongoing trials of the **Influenza A (H1N1) 2009 monovalent vaccine** in healthy children. We have also opted to stratify our study population into 3 groups based on age. The groups were selected to provide information across all age groups and with knowledge that there would be insufficient power to compare immune response across age groups. This study is limited to HIV-1 perinatally infected children and youth.

In order to understand the mechanism of disease and protection, we will investigate the seroresponse, duration of response, and development of influenza-like illness following vaccine in this population. We also propose investigation of the cell-mediated response to vaccine. The generation of cytotoxic T lymphocyte (CTL) responses against **2009 H1N1 Influenza A** is of particular interest, because this virus replicates better in lung tissue than seasonal influenza and CTLs are the major mediator of viral clearance in the lungs. Memory B cells to **2009 H1N1 Influenza A** will ensure that the host responds adequately to exposure to the wild type virus.

In summary, **2009 H1N1 Influenza A** is likely to infect a significant proportion of HIV-1 infected children and youth if an effective vaccine is not available

before infection is widespread. Infection will likely lead to severe disease in this vulnerable population, therefore, vaccine efforts are critical. Immunogenicity of the candidate **Influenza A (H1N1) 2009 monovalent vaccine** must be established in HIV-1 infected children in order to assure that this population is protected. Lack of a protective immune response would support the need for additional measures to protect this high risk population.

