## 8.6 Analyses

### 8.61 Primary Analyses

#### 8.611 Safety

The proportion of all subjects and of subjects within age strata experiencing grade 3 or grade 4 adverse events following the first and second doses of study vaccine will be presented. The precision with which these sample results estimate the rate of similar adverse events in the population represented by the study sample will be reported in terms of 90% confidence intervals (CI) around the sample proportions. This will provide 95% confidence that the rate of severe adverse effects is not greater than the upper limit of the CI around the proportion of subjects with grade 3+ events in the study sample.

Table 1 illustrates the confidence intervals for a range of hypothetical proportions of adverse events. This table shows (e.g.) that a sample finding of no grade 3+ adverse events in a total evaluable sample of 120 subjects would provide 95% confidence that the rate in the population from which the sample was drawn is no greater than 2%. A similar finding within a subsample of 20 subjects would provide 95% confidence that the population rate was no greater than 14%.

Table 1: Exact 90% Confidence Intervals around Potential Proportions of Subjects Exhibiting Grade 3+ Adverse Events (Total Sample and Selected Subsample Sizes)

| N   | Samples Rate | Lower Limit | Upper Limit |
|-----|--------------|-------------|-------------|
| 120 | 0%           | 0%          | 2%          |
|     | 5%           | 2%          | 10%         |
|     | 10%          | 6%          | 16%         |
|     | 25%          | 19%         | 32%         |
|     | 50%          | 42%         | 58%         |
| 40  | 0%           | 0%          | 7%          |
|     | 5%           | 1%          | 15%         |
|     | 10%          | 3%          | 21%         |
|     | 25%          | 14%         | 39%         |
|     | 50%          | 36%         | 64%         |
| 20  | 0%           | 0%          | 14%         |
|     | 5%           | 0%          | 22%         |
|     | 10%          | 2%          | 28%         |
|     | 25%          | 10%         | 46%         |
|     | 50%          | 30%         | 70%         |

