## 8.62 Key Secondary Analyses

Prediction of immune response will be addressed in secondary analyses. Since this is a new vaccine about which there is considerable uncertainty with respect to the distribution of antibody titers which it may elicit, alternative outcome variables will be explored. These include:

- 1) The log (10) HAI titer,
- 2) HAI titer >10, considered indicative of an immune response; and
- 3) HAI titer >40, which is considered to be likely to be protective.

The distribution of log (10) HAI titer will be examined to determine whether it satisfies the normality assumption required for linear regression analysis. If this is not true, then this method will be not be used. Since the other potential outcome

variables listed above are categorical, the method of analysis for those outcome variables will be logistic regression.

Factors predicting immune response will be examined on data collected after the first vaccination and, again, after the second. A primary predictor will be the age stratification factor. If immune response were to vary significantly across age strata, this would counter indicate pooling across age strata when presenting results. Additional potential predictors will include variables such as: CD4 count or percentage at baseline, viral load at baseline, HAI titers to the seasonal influenza vaccine, ARV treatment, and timing of seasonal influenza vaccine. Additional predictors may be explored as additional data concerning the H1N1 virus and the study vaccine become available.

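### The per-age-group figure of 40 means evaluable in the Schema but enrolled in 8.4, and pooling of immune response across age groups is tied to a comparison the plan itself calls underpowered

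*Combined protocol and SAP*

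**What the plan says.** **Stratum size.** Three places give a per-age-group figure of 40, with different meanings.

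- Schema, Stratification: "Subjects will be stratified by age (at least 40 evaluable subjects per group".
- Section 8.3: "Subjects will be stratified by age (at least 40 subjects per group", with no mention of evaluability.
- Section 8.4: "We will enroll at least 40 subjects each from three different age groups".

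The overall target is "140 children and youth to obtain at least 120 evaluable" in the Schema, and 8.4 agrees: "This sample size is expected to yield at least 120 evaluable". To be evaluable a subject needs both doses 21-28 days apart and every HAI sample through Day 10 after Dose #2 in window. No per-stratum yield is given. Section 4.7 mentions an enrollment cap, but its terms are kept on a website.

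**Reporting by age.** Section 8.611 presents adverse event proportions for all subjects and within age strata. Section 8.612 presents the immune response proportion without mentioning strata. Section 8.62 then says: "If immune response were to vary significantly across age strata, this would counter indicate pooling across age strata when presenting results". Section 1.22 says the age groups were chosen knowing that "there would be insufficient power to compare immune response across age groups".

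**The concern.** Age is the only stratification factor, and 1.22 gives information across the age range as its purpose. Two things weaken that purpose.

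First, a site network following 8.4 to the letter can finish with fewer evaluable subjects in an age group than the Schema sets, and nothing visible in the documents would flag it.

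Second, the only rule on whether the strata may be combined for immune response is a significance criterion. A comparison with low power will often be non-significant when the strata truly differ. With no commitment in 8.612 to show the strata, the report of a primary endpoint (8.214) could then be one pooled rate over groups that respond differently.

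**Working it through.** **Inputs.** 140 enrolled and at least 120 evaluable (Schema, 8.4); 40 per group (Schema, 8.3, 8.4); exact two-sided 90% intervals (title of Table 3; for safety, 8.611 says results "will be reported in terms of 90% confidence intervals (CI) around the sample proportions"). Assumptions not in the documents: the same evaluable fraction in every stratum, independent subjects, a two-sided 5% level for the age comparison, and the response rates used for power.

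**Reproducing the plan.** Clopper-Pearson limits are the 5% quantile of Beta(x, n−x+1) and the 95% quantile of Beta(x+1, n−x). For 20/40 this gives 36.1-63.9% (Table 3: 36-64%). For 30/40 it gives 61.3-85.8% (Table 3: 61-86%). All rows of Tables 1 and 3 reproduce to the printed rounding.

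**Enrolled against evaluable.**

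- Implied minimum yield: 120/140 = 0.857.
- 40 enrolled: 40 × 0.857 = 34.3 evaluable. For 20% to 5% non-evaluable the range is 32 to 38.
- A 40/40/60 accrual totals 140 and meets 8.4. Expected evaluable: about 34/34/51.
- Enrolment for 40 expected evaluable: 40/0.857 = 46.7, so 47 per group, or 47/47/46 within 140.

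**Effect on precision.** At n = 34, 17/34 gives 34.9-65.1%. The half-width rises from 13.9 to 15.1 points, a loss of 1.2 points.

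**Can an equal split secure 40 in every group?** P(all three ≥ 40) = P(Bin(47, y) ≥ 40)² × P(Bin(46, y) ≥ 40).

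| Yield y | 47 enrolled | 46 enrolled | All three |
|---|---|---|---|
| 85.7% | 0.645 | 0.508 | 0.21 |
| 90% | 0.907 | 0.828 | 0.68 |
| 92% | 0.968 | 0.928 | 0.87 |

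At 85.7%, for example, 0.645² × 0.508 = 0.21. Since 3 × 40 = 120 equals the overall evaluable target, a minimum of 40 evaluable in every group is harder to meet than 120 in total.

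**Power of the age comparison.** This is a three-group chi-square test on the binary response, 2 degrees of freedom, 40 per group. The noncentrality is n Σ(pᵢ − p̄)² / [p̄(1 − p̄)].

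- 65/75/80%: p̄ = 0.733, Σ = 0.01167, so 40 × 0.01167 / 0.1956 = 2.39; power 26%.
- 65/75/85%: p̄ = 0.75, Σ = 0.02, so 40 × 0.02 / 0.1875 = 4.27; power 44%.

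Simulation agrees to within about one point. With 34 per group the figures are 23% and 38%. A wide gap fares better: 50/75/75% gives 68% with 40 per group.

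**The case against.** **The by-age precision fails.** A reader might infer that the N=40 precision in Tables 1 and 3 will not be delivered. The documents do not support that. An even split of 140 gives about 40 expected evaluable per group, and nothing in the plan calls for 40/40/60. The 85.7% is a floor, because both places say at least 120; if it were the true rate, even the overall target would be met only 56% of the time. The N=40 rows illustrate selected subsample sizes, and 8.1 already disclaims precise estimates for all subgroups. The enrollment cap in 4.7 may control age groups; its terms cannot be seen. What stands is that the text does not secure the Schema's figure.

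**By-age safety is short too.** This does not follow. Section 8.611 covers all subjects, not only evaluable ones, so 40 enrolled and vaccinated supplies N=40 after Dose #1. The shortfall concerns evaluable immunogenicity data.

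**The pooling rule reduces stratum precision.** It does not. It changes neither the number per stratum nor the width of any interval; it bears only on how results are shown.

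**The pooling rule permits pooling after a non-significant result.** Read literally, 8.62 states only that a significant difference speaks against pooling. It does not say that non-significance licenses pooling or that stratum results would be suppressed, and 1.22 is open about power. This is a fair reply. But significance is the only criterion offered and 8.612 is silent on strata, so the inference is left open where one sentence would close it.

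**The power figures rest on assumptions.** They do. Section 8.62 names no test level and lists several outcomes, including log titer, which could have more power than a binary response.

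**Conclusion.** The concern holds in two separate parts.

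1. The Schema and 8.3/8.4 disagree on whether 40 per age group means evaluable or enrolled. An accrual that satisfies 8.4 can be expected to leave about 34 evaluable in a group at the implied minimum yield. The consequence for precision is small, about one point on each limit at 50% response. Within 140 subjects the Schema's minimum cannot be assured even with equal strata: the chance is about 21% at 85.7% yield, 68% at 90% and 87% at 92%, assuming a common yield across strata.

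2. The weightier part is reporting. Whether immune response is pooled across ages is tied to a significance criterion that the plan itself says lacks power, and by-age immunogenicity is not committed to as by-age safety is. The 26% and 44% illustrate the size of the problem under assumed rates and an assumed 5% level; the concession in 1.22 makes the point without them.

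**What to change.** **Sections 8.3 and 8.4, and the Schema.** Set near-equal accrual targets of about 47/47/46 within the existing 140, applied through the enrollment system or the cap in 4.7. Restate the Schema figure as about 40 expected evaluable per group. Keeping it as a firm minimum would need more subjects: about 50 enrolled gives one stratum a 91% chance of reaching 40 at 85.7% yield, and 3 × 50 = 150 exceeds the planned 140. A gain of about one point in half-width does not justify that. No new table rows are needed.

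**Sections 8.62 and 8.612.** Delete the significance-based pooling rule. State in 8.612 that response rates with exact 90% intervals are always reported by age stratum, after each dose, beside the pooled estimate. The regression on age in 8.62 can stay as a descriptive secondary analysis.

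**Cost.** Wording and stratum targets; no added subjects, visits or samples. Accrual may slow slightly in the scarcest age group, and the stated stratum figure becomes slightly less favourable.

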### 8.5 Safety Monitoring

It is the responsibility of the Protocol Team to interpret safety data and make decisions regarding adverse events to protect subjects from undue risk. In addition, the IMPAACT Network will appoint a Study Monitoring Committee (SMC) to provide independent reviews to ensure subject safety. The SMC is composed of three clinicians and a statistician independent of the P1088 protocol team and vaccine manufacturer.

It is required that the data needed for the toxicity reports be entered into the database within 48 hours of the time at which the results of the laboratory tests or clinical examinations become available.

Reports compiled by the Data Management Center (DMC) will be reviewed and discussed by the Protocol Team on biweekly conference calls while subjects are accruing and the vaccine is being administered. The Protocol Team will meet via conference call at least once a month after the last dose of study vaccine is given. These reports may also be reviewed by the Study Monitoring Committee, if any of the scenarios described below occur, or if any other conditions warrant such a review.

Adverse events will be monitored throughout the follow-up period. If the protocol team identifies any potentially treatment-related toxicity that may compromise subject safety, it will determine whether further enrollment and vaccinations will be paused. Should this occur, the Study Monitoring Committee will review all relevant data and will determine whether, and under what conditions, the study will be allowed to proceed or will be stopped. **For safety monitoring, a vaccine related SAE is an SAE that is judged to be “definitely”, “probably”, or “possibly related” to study vaccine.**

Further enrollment and vaccinations will be paused for SMC review and recommendation if any of the following are reported across this study or ongoing NIH studies evaluating the 30mcg dose of the Novartis **Influenza A (H1N1) 2009 monovalent vaccine**.

- Any death occurring within the 10 days following administration of study vaccine that was not the result of trauma or accident.
- Any subject having laryngospasm, bronchospasm, or systemic anaphylaxis within 24 hours of administration of study vaccine.
- Two or more subjects with generalized urticaria associated with product administration within 72 hours of administration of study vaccine.
- Any subject with any necrosis at the injection site.
- Three or more subjects with abscesses or ulcerations, associated with study vaccine administration.
- Any subject with a vaccine-related SAE, as defined by ICH, as mentioned in section 7.0.
- Any subject with acute weakness of limbs and or cranial nerve innervated muscles (description of potential signal of Guillain-Barre Syndrome).

The study will also be halted for SMC review and recommendation if, during the 10 days after each vaccination, any of the following occurs:

- 15% or more (minimum of 2 if less than 20 subjects have been vaccinated) of the subjects enrolled in this study experience the same severe (Grade 3 or higher by

the DAIDS Toxicity Table) vaccine-related local reaction that interferes with daily activities. Dimensions of a local reaction are not included in stopping decisions.

- 15% or more (minimum of 2 if less than 20 subjects have been vaccinated) of the subjects in this study experience the same severe (Grade 3 or higher by the DAIDS Toxicity Table) vaccine-related quantitative systemic reactions.
- 15% or more (minimum of 2 if less than 20 subjects have been vaccinated) of the subjects enrolled in this study experience the same severe (Grade 3 or higher by the DAIDS Toxicity Table) vaccine-related subjective systemic reactions, the severity (grade) of which is corroborated by study personnel.

If the study is stopped for any of the above reasons, the SMC will instruct the protocol team under what conditions the study would stop again for a repeat of the same reason.

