### 3.0 STUDY DESIGN

This is a multi-center, open label, Phase II study in 140 children and youth, aged  $\geq 4$  years to  $<25$  years old in the US and Puerto Rico, who were infected with HIV-1 via perinatal transmission. The purpose of the study is to investigate the safety, reactogenicity, and immunogenicity of a two dose regimen of **Influenza A (H1N1) 2009 monovalent vaccine**.

Subjects do not need to be receiving ARV therapy but if they are receiving ARVs, they must have been on a stable ARV regimen for at least 90 days prior to vaccination with no intention to modify the regimen within the next 60 days. Changes in dosage due to weight changes or formulation are acceptable. The site should contact the team ([[contact]](mailto:[contact])) for other modifications. Additionally, if they are not currently receiving ARVs, the subject should not have received ARVs within 90 days prior to vaccination nor plan to initiate ARVs within the next 60 days.

STEP I: Subjects who meet the entry criteria for the study will receive **Influenza A (H1N1) 2009 monovalent vaccine**, 30 mcg, administered as TWO 15mcg IM injections, in either the deltoid muscle(s) or antero-lateral thigh muscle(s).\* Dose #1 will be administered on Day 0.

STEP II: Eligible subjects will receive a second dose of **Influenza A (H1N1) 2009 monovalent vaccine**, 30 mcg, administered as TWO 15mcg IM injections, in either the deltoid muscle(s) or antero-lateral thigh muscle(s).\* Dose #2 will be administered on Day 21 (+ 7 day window).

\*Only children and teens (4-18 years) may receive an injection in the antero-lateral thigh muscle (refer to the table in section 5.12 "Injection Site and Needle Size").

NOTE: For women who are found to be pregnant after receiving study vaccine Dose #1 but before study vaccine Dose #2, STEP II will be deferred until the woman is  $\geq 14$  weeks gestation. These women and their infant(s) will be followed as described in Appendix IB. Women who become pregnant after the second dose of vaccine will continue to be followed as outlined in Appendix IA.

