4.3 Inclusion Criteria for STEP II

- 4.31 Received the first dose of **Influenza A (H1N1) 2009 monovalent study vaccine** at least 21 days ago.
- 4.32 Has a documented platelet count of  $>50,000$  per  $\text{mm}^3$  and an ANC of  $>500$  per  $\text{mm}^3$  within the 30 days prior to Step II entry.
- 4.33 Females of child-bearing potential must have a negative pregnancy test within 72 hours of Step II entry.

OR

If a woman became pregnant after Dose #1, she must be  $\geq 14$  weeks of gestation and have her obstetrician's permission to receive the vaccine.

NOTE: For management of women, who become pregnant after Dose #1, see section 6.7.

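### The 15% halting rule covers each vaccination but divides by subjects enrolled, so read literally its bar sits well above 15% while Dose #2 is being rolled out

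*Combined protocol and SAP*

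**What the plan says.** The lead-in to the rate-based rules in Section 8.5 ties them to each dose: "The study will also be halted for SMC review and recommendation if, during the 10 days after each vaccination", one of three conditions occurs. The bullets on local reactions and on subjective systemic reactions use "15% or more (minimum of 2 if less than 20 subjects have been vaccinated) of the subjects enrolled in this study". The bullet on quantitative systemic reactions leaves out *enrolled* and reads "of the subjects in this study experience the same severe". In all three, the parenthesis that sets a floor of 2 refers to subjects *vaccinated*.

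Section 8.4 plans "Approximately 140 children and youth" and states: "Accrual is anticipated to be 4-6 weeks". Section 3.0 schedules Dose #2 at Day 21 with a 7-day window, and Section 4.3 requires that the first dose was given "at least 21 days ago". No section gives a denominator specific to a dose, or says whether Dose #1 and Dose #2 reactions are pooled.

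**The concern.** One sentence uses three reference groups: events after each vaccination, subjects enrolled, and subjects vaccinated. Dose #1 is given at entry, so for that dose the groups are almost the same people. When Dose #2 begins, most enrolled subjects have not yet had it, but they remain in the denominator. Subjects whose second dose is withheld under Section 4.4 or deferred under Sections 6.3 and 6.7 also remain.

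Section 2.1 makes safety after each of the two doses a primary objective, and Section 8.611 reports Grade 3 and 4 events following the first and second doses. A monitoring rule whose effective bar differs between doses, and drifts by calendar day for Dose #2, does not serve that objective as its stated 15% suggests.

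**Working it through.** **The plan's own figures.** The documents give no trigger count or operating characteristic for this rule, so there is no figure of that kind to reproduce. The nearest probability statement, Table 2 in Section 8.611, reproduces with an exact binomial at N = 120. For example, a 2% rate gives 1 − 0.98^120 = 0.91 for one or more events (stated 91%), and a 3% rate gives 0.878 for two or more (stated 88%).

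**Inputs.** 140 subjects and 4-6 weeks of accrual (Section 8.4); Dose #2 from 21 days after Dose #1 (Sections 3.0 and 4.3); 15% of subjects enrolled (Section 8.5).

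**Assumptions.** Uniform accrual over w weeks, Dose #2 at exactly 21 days in every subject, Dose #2 reactions counted alone, and each reaction known on the day of dosing. Giving every subject Dose #2 and allowing no reporting delay both favour the rule as written.

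**Formulas at study day t**
- Enrolled: E = min(140, 140t/7w)
- Dose #2 recipients: R = min(140, 140(t − 21)/7w)
- Events needed: K = 0.15 × E, rounded up

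| Study day | Accrual | E | R | K | K/R |
|---|---|---|---|---|---|
| 24 | 4 wk | 120 | 15 | 18 | not reachable |
| 24 | 5 wk | 96 | 12 | 15 | not reachable |
| 24 | 6 wk | 80 | 10 | 12 | not reachable |
| 28 | 4 wk | 140 | 35 | 21 | 60% |
| 28 | 5 wk | 112 | 28 | 17 | 61% |
| 28 | 6 wk | 93.3 | 23.3 | 14 | 60% |
| 35 | 4 wk | 140 | 70 | 21 | 30% |
| 35 | 5 wk | 140 | 56 | 21 | 37.5% |
| 35 | 6 wk | 116.7 | 46.7 | 18 | 39% |

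Only when all 140 have had Dose #2 does the requirement equal the stated rate: 21/140 = 15%.

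**Length of the unreachable period.** Let s be days since the first Dose #2 and r the daily accrual. The rule becomes reachable when r·s ≥ 0.15·r·(21 + s), that is 0.85s ≥ 3.15, so s ≥ 3.7 days. The rate r cancels, so the result is the same for 4, 5 or 6 weeks.
- If every Dose #2 falls at Day 28, the period is 4.2 days for 4-week accrual (21 events at 5 recipients per day) and about 4.9 days for 5 or 6 weeks (0.85s ≥ 4.2).
- If accrual is strongly front-loaded (cumulative enrolment proportional to the square root of time), it is about 0.5 day.
- If accrual is back-loaded (proportional to time squared), it is about 11-13 days.
- Across these cases, roughly 12-21 Dose #2 recipients are needed before the rule can be met.

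**The floor of 2.** At 140/28 = 5 or 140/42 = 3.33 entries per day, the 20th subject has had Dose #1 by day 4 or day 6. Read literally, the floor has lapsed well before day 21, when 70 to 105 subjects are enrolled.

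**Illustration of the dilution.** Suppose half of Dose #2 recipients have the same severe reaction. After seven days of Dose #2 dosing, the probability that the rule as written is met is 15.5% (21 or more of 35) or 20.2% (14 or more of 23). The probability that at least 15% of those recipients are affected exceeds 99.9% in both cases. This shows the size of the effect and does not propose a threshold.

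**If Dose #1 reactions also count.** On day 24 the shortfall is 18 − 15 = 3, 15 − 12 = 3 or 12 − 10 = 2 subjects. That many Dose #1 reactors among subjects not yet given Dose #2 would make the rule reachable, though still only if every Dose #2 recipient reacted.

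**The case against.** The best defence is that the text does not fix the reading on which the arithmetic depends. If the rule is cumulative by subject, so that anyone with the reaction after either dose counts once, a study-wide denominator is coherent and earlier Dose #1 events bring the trigger closer. The floor sits under a lead-in about each vaccination, so *vaccinated* could mean vaccinated with that dose; if two events were then enough, the early gap would close. The wording *enrolled in this study* may also be there only to separate these bullets from the preceding list, which counts events across other NIH studies as well.

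All of this stands as a reason to make the finding conditional. None of it settles the denominator. Appendix IA, footnote 17, refers explicitly to enrolment in Step II where Step II is meant; Section 8.5 does not.

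The unreachable period is also short and depends on the accrual shape. With contact around Day 2, 48 hours allowed for data entry and biweekly team calls, much of a 3-4 day gap would pass before review under any denominator. That is fair, and it makes the raised bar on days 28 to 35 the more important result.

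Finally, Section 8.5 has other protections. A single vaccine-related serious event, anaphylaxis, injection-site necrosis or acute weakness pauses the study, and the team may pause for any potentially treatment-related toxicity. Section 6.2 asks subjects with possibly vaccine-associated Grade 3 or 4 events to return within 72 hours. A reader might infer that early Dose #2 recipients are unprotected; these provisions show otherwise. They do not, however, supply another rate-based trigger for non-serious severe reactions such as pain or fever.

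**Conclusion.** The concern holds as a wording defect with a material effect on Dose #2 monitoring. On the literal text, the bar moves from unreachable, to about 60% of recipients, to 30-39%, against a stated 15%. This rests on counting Dose #2 reactions alone and on uniform accrual; the documents give only the 4-6 week range.

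Three stronger conclusions are tempting but unsupported:
- A reader might infer that the rule simply cannot work early in Dose #2. That depends on the counting convention and the accrual shape, neither of which the documents fix.
- A reader might infer that the floor of 2 never restarts for Dose #2. That is the literal reading, but the text is unclear rather than explicit.
- A reader might regard Dose #2 as the untested part of the regimen. It is the same product and amount as Dose #1 (Section 5.11), and Section 3.0 notes other ongoing studies that include 30 mcg doses.

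**What to change.** The sponsor should reconcile *enrolled*, *in this study* and *vaccinated* across the three bullets of Section 8.5 so that numerator and denominator refer to the same subjects. The text should then state two things: whether reactions are counted separately for each dose or cumulatively by subject, and whether the fewer-than-20 floor applies to each dose. Which rule to adopt is the sponsor's decision. No change to review frequency is proposed; the 48-hour requirement in Section 8.5 is a data-entry deadline, not a review cycle.

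The cost is wording in three bullets. Depending on the choice made, there may be a somewhat higher chance of a pause for committee review.
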